### Statistical analysis and power analysis

2.7

All analyses will be performed using SPSS for Windows, version 16, and GraphPad InStat. Analysis of variance is used for comparing mean values of patient's age, weight, height, and body mass index. For non-parametric measures like VAS and WOMAC, differences between baseline and post-treatment scores for each group are computed by the Wilcoxon signed ranks test. The difference between each treatment group is performed by the Kruskal–Wallis test. The level of statistical significance is set as *P* < .05. A power analysis is conducted to estimate the requisite sample size. From previous studies, a clinically significant difference reduction in the VAS was defined as 3 cm; a standard deviation of 3.49, probability of a Type I error of 0.05 and power of 0.8 resulted in an estimated sample size of 15. Consequently, a total of 120 subjects will be recruited.

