### Participants

2.1

Subjects will be included in this study if they

1.have painful knee osteoarthritis for at least 6 months with degenerative osteoarthritic knee of grade 2 to 3 or less based on radiographic diagnosis in the Kellgren and Lawrence grading of osteoarthritis,2.have no limitation of range of motion (ROM) except for minimum tightness in the knee joint,3.do not engage in any high-joint-loading exercises such as hiking or tennis playing and have not undergone any specific treatments 3 months before entering the study,4.have a minimum score of 25 on the Western Ontario and McMaster Universities Osteoarthritis Index (WOMAC) total score, and5.have a knee pain ≥4 on the visual analog scale (VAS) in the previous 3 months.

Subjects will be excluded from the study at pretreatment evaluation if they have any other musculoskeletal problems associated with the knee joint, such as fracture, tendon or ligament tears, meniscus injury, rheumatoid arthritis, or knee surgery. Patients will be also excluded if they have musculoskeletal problems associated with the hip or ankle/foot joints, have central or peripheral neuropathy, or have received physical therapy and/or intra-articular corticosteroid or hyaluronic acid injections during the last 6 months.

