### Random allocation

2.3

Before starting the study, a randomization list is produced using software-generated randomized numbers; the randomization depends on random blocks of 10 (Table 1). Patients will not know to which group they are assigned or which treatment they will be offered. Patients will be assigned at random to the ultrasound + LLLT group, LLLT group, or the ultrasound group. Participants are enrolled by the research assistant. After baseline examination, all patients will be given a full explanation of the treatment protocol and will be required to sign a written informed consent for study participation and for publication of the results. All the data collectors, surgeons, statistical analysts, as well as result assessors are not aware of grouping assignment (Fig. 1).

**Table 1 T1:** Patient baseline demographics.

Demographics	Combined group	LLLT group	Ultrasound group	*P* value
Number of patients (knees)				
Age at surgery^∗^ (years)				
Male sex (no. [%])				
BMI^∗^ (kg/m^2^)				
Right side (no. [%])				
Follow-up^∗^ (years)				

BMI = body mass index, LLLT = low-level laser therapy.

∗ The values are given as the mean and the SD.

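### Section 2.7 plans within-arm Wilcoxon tests beside a between-arm Kruskal–Wallis test at the same P < .05 and does not say which decides; with three active arms, the within-arm tests cannot isolate a device effect.

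*Protocol article*

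**What the plan says.** Section 2.7 of the protocol article names two analyses for VAS and WOMAC. Within arms, "differences between baseline and post-treatment scores for each group are computed by the Wilcoxon signed ranks test". Between arms, "The difference between each treatment group is performed by the Kruskal–Wallis test". One level covers both: "The level of statistical significance is set as" P < .05. The section does not rank the two tests, and it does not say whether the Kruskal–Wallis test is run on change or on final scores.

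Two other parts of the design bear on this:

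- Entry (section 2.1) sets a floor on the same two scales. Subjects must "have a minimum score of 25 on the Western Ontario and McMaster Universities Osteoarthritis Index (WOMAC) total score" and "have a knee pain ≥4 on the visual analog scale (VAS) in the previous 3 months".
- Allocation (section 2.3): "Patients will be assigned at random to the ultrasound + LLLT group, LLLT group, or the ultrasound group". Every arm receives at least one modality, and there is no sham, untreated or waiting arm.

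Section 2.5 defines the primary outcome as change in VAS from baseline. The hypothesis, in the Introduction and again in the Discussion, is a difference between groups. Table 2 has a single P value column across the three arms.

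**The concern.** The signed-rank test asks whether scores in an arm moved. In this trial they may well move even if neither device does anything. Patients come in with raised scores, they expect to improve, and knee pain fluctuates. A significant within-arm result therefore shows change but not its cause, and no arm lets the nonspecific part be subtracted.

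The randomised comparison does not have this weakness, because a fall common to all arms cancels out. But the plan puts the two tests side by side at one level and ranks neither. A likely result when nothing works is a non-significant Kruskal–Wallis test beside one or more significant Wilcoxon tests. Section 2.7 does not say how that should be read. What is at stake is whether such a result is later reported as evidence that ultrasound, LLLT or both relieve pain.

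**Working it through.** **Inputs from the protocol article.** Section 2.7 gives a VAS difference of 3 cm, SD 3.49, type I error 0.05, power 0.8, a stated n of 15 and a total of 120. Section 2.1 gives the VAS floor of 4. **Assumptions:** equal allocation, so 120 / 3 = 40 per arm; two-sided tests; 3.49 taken as the SD of change.

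**Step 1. The plan's own figure.** The text reads "a clinically significant difference reduction in the VAS was defined as 3 cm; a standard deviation of 3.49", and "probability of a Type I error of 0.05 and power of 0.8 resulted in an estimated sample size of 15". It does not say whether 15 is per arm, or whether the difference is within or between arms.

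- Paired, two-sided, normal formula: n = [3.49 × (1.960 + 0.842) / 3]² = 10.6, so 11. The exact paired t test gives 13, and allowing for the Wilcoxon test's efficiency gives 14 (0.955) or 16 (0.864).
- Two-sample, two-sided: n = 2 × 10.6 = 21.2, so 22 per arm (exact t: 23).
- Two-sample, one-sided: n = 2 × [3.49 × (1.645 + 0.842) / 3]² = 16.7, so 17 per arm.

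None of these gives exactly 15. It lies closest to a two-sided paired calculation, but the one-sided two-sample formula is also near. This hints that the within-arm test carries weight in the plan; it does not prove it.

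**Step 2. A common nonspecific fall, no treatment effect.** The standard error of an arm's mean change is 3.49 / √40 = 0.552 cm. By a t test, an observed mean fall of 2.023 × 0.552 = 1.12 cm reaches P < .05. Three identical arms of 40 were simulated, with change normal and SD 3.49:

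| Common fall (cm) | One arm significant for improvement (Wilcoxon) | At least one of three arms | Kruskal–Wallis on change |
|---|---|---|---|
| 0 | 2% | 7% | 5.3% |
| 0.5 | 14% | 36% | 4.6% |
| 1.0 | 40% | 79% | 5.1% |
| 1.5 | 73% | 98% | 5.0% |
| 2.0 | 93% | 100% | 5.1% |

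The nominal rate in the direction of improvement is 2.5% per arm. As a check on the third row, 1 − (1 − 0.404)³ = 0.79.

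**Step 3. Regression to the mean alone.** Suppose patients are selected on a baseline reading of at least 4 from a population with mean μ, SD 2 and test-retest correlation ρ. The expected fall on retest is (1 − ρ) × 2 × φ(a) / [1 − Φ(a)], with a = (4 − μ) / 2. For μ = 4 and ρ = 0.5 this is 0.5 × 2 × 0.399 / 0.5 = 0.80 cm. Simulation with 40 per arm and scores held to 0–10 gave the following (mean fall, then share of trials in which an arm is significant for improvement):

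| Population mean | ρ = 0.5 | ρ = 0.7 | ρ = 0.9 |
|---|---|---|---|
| 4 | 0.80 cm, 75% | 0.48 cm, 51% | 0.16 cm, 19% |
| 5 | 0.51 cm, 37% | 0.30 cm, 23% | 0.10 cm, 10% |
| 6 | 0.29 cm, 15% | 0.17 cm, 10% | 0.06 cm, 6% |

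Adding a further common fall of 0.5 cm raises the per-arm rate to 71%–99%; adding 1.0 cm raises it to 99%–100%. Across all these settings the Kruskal–Wallis test on change rejected in 3.5% to 6.1% of trials, which is 5% within simulation error.

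The SD of change in Step 3 is about 0.9 to 1.9, well below 3.49. The same fall would reach significance less often at the SD used in Step 2.

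**The case against.** The case for leaving the plan alone is substantial. The sentence after the Wilcoxon sentence plans a valid between-arm test that keeps its level. The aim is synergy of the combination, the hypothesis is between groups, and Table 2 has no place for a within-arm P value. Defining the outcome as change from baseline fixes the variable to be analysed, not the test. The signed-rank test is also a valid test of whether scores changed; it goes wrong only when given a causal reading.

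All of that stands, and it rules out a stronger reading that a reader might infer: that the plan lets any arm be declared effective, or that the within-arm P values are themselves invalid. The documents do not support this. No sentence says that a significant within-arm test will be taken as efficacy.

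The figures also have limits. The VAS floor refers to pain over the previous three months, which need not be the baseline reading that is tested. If it is a separate earlier reading, regression between baseline and follow-up is smaller or absent. At a correlation of 0.9, regression alone gives only 6% to 19%, so regression by itself does not ensure a significant result. The WOMAC floor was not simulated. The 40% to 93% figures assume a nonspecific fall and show how often it would be detected; they do not show that it will occur.

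What the objection does not remove is the missing ranking. Two tests share one level, and only one of them answers the trial's question.

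**Conclusion.** The point holds in a limited form. Section 2.7 does not say which test decides, and one of the two cannot support a claim about a device in a trial whose arms are all active. With no treatment effect, 40 per arm and 3.49 as the SD of change, a common nonspecific fall of 1.0 to 2.0 cm makes an arm significant in about 40% to 93% of trials. Regression to the mean alone gives about 6% to 75% per arm, assuming SD 2, population mean 4 to 6, correlation 0.5 to 0.9 and selection on the baseline reading itself. The planned Kruskal–Wallis test, run on change, stays near 5% throughout.

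The population mean, SD 2, the correlation, the size of the nonspecific fall and equal allocation are assumptions, not protocol figures. The qualitative conclusion does not depend on them: without a sham or untreated arm, a within-arm P value cannot attribute change to treatment.

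**What to change.** State in section 2.7 that inference rests on the randomised between-arm comparison of change from baseline, using the Kruskal–Wallis test already planned. Report each arm's change on VAS and WOMAC descriptively, as a median or mean with a 95% CI and no P value. Add one sentence saying that within-arm change includes nonspecific improvement and is not evidence for a device. That sentence matters because an interval that excludes zero invites the same misreading as a small P value.

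This changes wording only. Recruitment, treatment and data collection are unaffected, and fewer tests are run. The small downside is the loss of within-arm P values that some readers may expect.

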### Primary outcome

2.5

The primary outcome is weekly change in pain intensity relative to baseline through 6 weeks of therapy, as measured on the VAS (0 = no pain, 10 = extreme pain). The VAS pain scale has been validated for consistency and reliability to assess pain associated with a variety of conditions, including osteoarthritis. Patients records their pain 4 hours after applying the device during daily treatment.

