### Secondary outcomes

2.6

Secondary outcome measures assessed are change in WOMAC score for pain stiffness and function, ROM, and muscle strength assessed at baseline and the end of the study. ROM and strength measurements are acquired by trained clinic staff on a small pilot cohort of sequentially enrolled patients using computerized dual inclinometry ROM and muscle tester equipment (JTECH Medical, Midvale, UT). To assess ROM, 1 inclinometer is positioned on the quadricep muscle at mid femur and the other at mid-tibia. Patients are asked to lay flat on their back and lift their leg and flex at the knee to measure flexion. Patients are then asked to sit at the edge of the table and extend their leg to measure extension. To assess muscle strength, a manual muscle tester is used. Patients are asked to sit at the edge of the table with their knee at approximately 90 degrees. The manual muscle tester is positioned and hold at anterior mid tibia while patients are asked to extend their leg to measure extension strength. To measure flexion strength, the muscle tester is held at anterior mid-tibia and the patient is asked to flex at the knee. Each ROM and muscle strength test is repeated 3 times and the average is recorded (Table 2).

**Table 2 T2:** Postoperative outcomes.

Outcomes	Combined group	LLLT group	Ultrasound group	*P* value
VAS				
WOMAC				
ROM				
Muscle strength				

LLLT = low-level laser therapy, ROM = range of motion, VAS = visual analog scale, WOMAC = Western Ontario and McMaster Universities Osteoarthritis Index.

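### The only between-arm test for VAS and WOMAC is an unadjusted Kruskal–Wallis test on an unnamed variable; adjusting for baseline would add precision at almost no cost

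*Protocol article*

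**What the plan says.** Section 2.5 of the protocol article defines the primary endpoint as a change score: "The primary outcome is weekly change in pain intensity relative to baseline through 6 weeks of therapy". Section 2.6 also defines the WOMAC endpoint as a change.

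Section 2.7 treats VAS and WOMAC as non-parametric measures and gives two procedures. Within arms, "differences between baseline and post-treatment scores for each group are computed by the Wilcoxon signed ranks test". Between arms, "The difference between each treatment group is performed by the Kruskal–Wallis test". The second sentence does not name the variable that enters the test.

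Table 2, titled "Postoperative outcomes", has rows labelled VAS and WOMAC (not change in either), one column per arm and one P value column. The article contains no model for VAS or WOMAC with baseline as a covariate.

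**The concern.** The trial's question is whether combined treatment does better than either modality alone, which is a between-arm question. Each patient's baseline VAS and WOMAC will be on file, and baseline pain usually predicts later pain. A Kruskal–Wallis test has no place for a covariate, so the randomised comparison cannot make best use of that information.

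The two possible readings fail in different ways:

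- **Post-treatment scores** (the Table 2 labels point this way). Baseline is ignored and the tested quantity is not the one defined in Section 2.5. A chance baseline difference carries through in favour of the arm that started lower.
- **Changes** (Section 2.5 points this way). The full baseline is subtracted. That is the right amount only if the regression slope of follow-up on baseline is 1.

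At stake are power for a modest difference between active arms and protection against chance imbalance in baseline pain.

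**Working it through.** **Inputs from Section 2.7.** Difference: "a clinically significant difference reduction in the VAS was defined as 3 cm". Spread: "a standard deviation of 3.49", not said to be of scores or of changes. Total 120 in three arms, taken as 40 each (the allocation ratio is not stated).

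**Assumed, not in the article.** Baseline to follow-up correlation rho of 0.3 to 0.7; 3.49 as the SD of the follow-up score; baseline SD either 3.49 or 1.73; a 2 cm benefit in one arm as the smaller effect; unbounded normal data.

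**Step 1: the plan's own figure.** The article states "probability of a Type I error of 0.05 and power of 0.8 resulted in an estimated sample size of 15".
- Two-sided comparison of two arms: 2 × (3.49 × (1.960 + 0.842) / 3)² = 21.2, so 22 per arm.
- The same, one-sided: 16.7, so 17.
- Paired t test, two-sided: 12.7, so 13. Divided by the minimum Wilcoxon efficiency: 12.7 / 0.864 = 14.7, so 15.

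The exact match is a within-arm signed-rank calculation. This does not prove that the figure was derived that way, and nothing below depends on it. That 3 × 15 = 45 rather than 120 is a separate matter.

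**Step 2: what stays of a chance baseline difference.** The slope is b = rho × SD_post / SD_baseline. If two arms differ by D at baseline, post-treatment scores retain b × D and changes retain (b − 1) × D; ANCOVA estimates b and removes the difference on average. With 40 per arm, D has standard error √(2/40) = 0.22 baseline SD, and exceeds 0.3 SD in either direction with probability 18%. For D = 0.3 SD:
- Baseline SD 3.49 (D = 1.05 cm): b = 0.3, 0.5, 0.7. Post-treatment scores retain 0.31, 0.52, 0.73 cm; changes retain −0.73, −0.52, −0.31 cm.
- Baseline SD 1.73 (D = 0.52 cm): b = 0.61, 1.01, 1.41. Post-treatment scores retain 0.31, 0.52, 0.73 cm; changes retain about −0.2, 0.0, +0.2 cm.

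So the direction of the remainder on changes depends on the slope.

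**Step 3: variance.** With equal SDs, relative variances are 1 (post-treatment), 2(1 − rho) (change) and 1 − rho² (ANCOVA). For rho = 0.3, 0.5, 0.7, the variance relative to ANCOVA is 1.10, 1.33, 1.96 for post-treatment scores and 1.54, 1.33, 1.18 for changes. The adjusted total that matches 120 unadjusted patients is 110, 90, 62 against post-treatment scores and 78, 90, 102 against changes.

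With baseline SD 1.73, the change variance 3.49² + 1.73² − 2 × rho × 3.49 × 1.73 is 11.55, 9.14, 6.72, against 3.49² × (1 − rho²) = 11.08, 9.14, 6.21 for ANCOVA. The ratios are 1.04, 1.00, 1.08, so little is left to gain over changes.

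**Step 4: simulated power (%), 40 per arm.** KW is Kruskal–Wallis.

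| Setting | rho | KW post | KW change | Rank ANCOVA | ANCOVA |
|---|---|---|---|---|---|
| 2 cm, equal SDs (2,000 runs) | 0.3 | 73 | 58 | 77 | 79 |
| | 0.5 | 73 | 72 | 83 | 87 |
| | 0.7 | 72 | 92 | 94 | 96 |
| 2 cm, baseline SD 1.73 (1,500 runs) | 0.3 | – | 74 | 75 | 78 |
| | 0.5 | – | 85 | 83 | 87 |
| | 0.7 | – | 94 | 94 | 96 |
| 3 cm, equal SDs (3,000 runs) | 0.3 | 98 | 91 | – | 99 |
| | 0.5 | 97 | 97 | – | 100 |
| | 0.7 | 98 | 100 | – | 100 |

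Repeat runs agreed within one or two points, and their extremes give the rounded ranges in the verdict. With no effect, all methods rejected in 4 to 6% of trials. Part of ANCOVA's lead is the F test's advantage over ranks on normal data; rank ANCOVA is the like-for-like comparison.

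**The case against.** **The pairing may already enter the between-arm test.** The primary and WOMAC outcomes are defined as changes, and the Kruskal–Wallis sentence directly follows one about baseline to post-treatment differences. Table 2 is an empty shell with short labels. This stands. A reader might infer that the pairing is used only within arms, so that the primary outcome is never compared between arms. The text does not settle that: the variable is simply not named.

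**Change scores need not over-correct.** A reader might infer that subtracting baseline over-corrects whenever the correlation is below 1. That holds only with equal SDs. Entry requires VAS of at least 4 on a 0 to 10 scale; a variable confined to 4 to 10 has an SD of at most 3.0, and a uniform spread gives 6/√12 = 1.73. The criterion refers to the previous 3 months, so this bounds the baseline value only approximately. With an SD near 1.73 the slope can pass 1 and the gain over changes nearly disappears. This stands and narrows the point.

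**It is efficiency, and 120 patients suffice at 3 cm.** This also stands. Randomisation protects the type I error, and the larger gains need an assumed smaller effect. But all three arms receive active treatment, so a difference below 3 cm is plausible.

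**Covariate adjustment belongs in an analysis plan.** This carries less weight. Section 2.7 names the between-arm test, and the named test cannot take a covariate.

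**Conclusion.** The point holds as one of precision and clarity. The between-arm variable is unspecified, and the named test cannot adjust for a baseline that the trial collects anyway.

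At 40 per arm and an assumed 2 cm difference, with rho 0.3 to 0.7 and 3.49 as the follow-up score SD:
- over Kruskal–Wallis on post-treatment scores, ANCOVA gains about 6 to 26 points and rank ANCOVA about 3 to 24;
- over Kruskal–Wallis on changes, ANCOVA gains about 4 to 21 points if baseline and follow-up SDs are equal, but only about 2 to 5 (rank ANCOVA about nil) if the baseline SD is about half.

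At the plan's own 3 cm, unadjusted power is already about 91% or more. It would be wrong to infer that the planned comparison is invalid or that 120 patients are too few for 3 cm; neither follows. The size rests on the assumed correlation, SD ratio, equal allocation and normal data, none of which the article gives.

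**What to change.** In Section 2.7, make the between-arm analysis of VAS and WOMAC a comparison of follow-up score by arm, adjusted for the patient's own baseline score. Use ANCOVA with the adjusted mean difference and 95% CI, or Quade rank ANCOVA if a non-parametric test is preferred. Apply it to the VAS time point or weekly summary that defines the primary outcome in Section 2.5, and name that time point or summary. State in a Table 2 footnote that the VAS and WOMAC P values come from this analysis, and keep the within-arm signed-rank tests as descriptive.

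The cost is a few sentences and a footnote. No new data or patients are needed, and SPSS, the package already named, can fit it. The downside is one covariate degree of freedom and, for ordinary ANCOVA, a linearity assumption.

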To our knowledge, only Paolillo et al tried to evaluate the synergistic effects of ultrasound and LLLT in patients with knee osteoarthritis. However, the sample size of their study was too small to draw convincing conclusions, thus further research is needed to confirm the synergies.^[13]^ Therefore, we will conduct this present randomized double-blind study to evaluate the synergistic effects of simultaneously applying ultrasound plus LLLT on pain and muscle function in patients with knee osteoarthritis. It is assumed that there will be a remarkable difference in postoperative outcomes between the intervention and control groups.

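### The stated tests do not compare the combination with LLLT alone or with ultrasound alone, so a significant result cannot support a claim for the combination

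*Protocol article*

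**What the plan says.** The Introduction gives the aim as to "evaluate the synergistic effects of simultaneously applying ultrasound plus LLLT on pain and muscle function in patients with knee osteoarthritis". Section 2.3 sets out the arms: "Patients will be assigned at random to the ultrasound + LLLT group, LLLT group, or the ultrasound group". There is no sham or untreated arm. The Introduction and Discussion also expect a difference between intervention and control groups, but no arm is named as control.

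Section 2.7 names two procedures for VAS and WOMAC. Within arms, "differences between baseline and post-treatment scores for each group are computed by the Wilcoxon signed ranks test". Between arms, "The difference between each treatment group is performed by the Kruskal–Wallis test". The threshold is "The level of statistical significance is set as *P* < .05", with no sidedness and no order of testing among comparisons. Table 2 in section 2.6 is laid out as "Outcomes Combined group LLLT group Ultrasound group *P* value", that is, three group columns and a single P value for each outcome.

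**The concern.** With these three arms, any claim for the combination needs at least two comparisons: against LLLT alone and against ultrasound alone. A three-group Kruskal–Wallis test makes neither. It has no direction and rejects when any arm differs from another, including when the two single modalities differ and the combination merely matches the better one.

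The within-arm Wilcoxon tests do not fill the gap. They compare no arms, so they make no use of the randomisation. They respond to natural course, placebo response and regression to the mean as well as to treatment. A significant change in the combined arm beside a non-significant one elsewhere is not evidence that the arms differ.

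At stake is the main conclusion: the planned P value could be significant when the combination adds nothing to one of its components, or is worse than both.

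**Working it through.** **Inputs from section 2.7.** VAS difference 3 cm, SD 3.49, type I error 0.05, power 0.8, stated sample size 15, total recruited 120.

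**Assumptions.** Equal allocation, so 120 / 3 = 40 per arm. Changes are normal, 3.49 is the SD of change, and each patient has one change score. (The protocol defines the primary outcome as weekly change over 6 weeks.)

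**1. The plan's own figure of 15.**
- Two arms, two-sided: n = 2 × (1.96 + 0.84)² × 3.49² / 3² ≈ 21.2, so 22 per arm. One-sided: 17 per arm.
- Three-arm analysis of variance: 21 per arm if one arm differs by 3 cm; 28 per arm if the means are 0, 1.5 and 3.
- Within one arm, paired t, two-sided: 12.68, so 13. Divided by a Wilcoxon efficiency of 0.864: 12.68 / 0.864 = 14.7, so 15.

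Of these variants only the within-arm one gives exactly 15. The article does not say how 15 was obtained or whether it is per arm or in total, and 3 × 15 = 45 does not lead to 120. The figure therefore gives no sign that the trial was sized for a comparison of the combination with a named arm.

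**2. Power of one contrast at 40 per arm.** SE = 3.49 × √(2/40) = 0.780. For 3 cm, 3 / 0.780 = 3.84, and Φ(3.84 − 1.96) = 97.0%.

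**3. What each rule does.** Simulated trials, 40 per arm, SD 3.49. The two-contrast rule requires both Mann–Whitney tests to be significant at two-sided 0.05 in favour of the combination. A range is the spread over repeated simulations of 3,000 to 6,000 trials.

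| True situation | Kruskal–Wallis rejects | Both contrasts favour combination |
|---|---|---|
| All arms equal | 4.9% | 0.5% |
| Combination = LLLT, ultrasound 3 cm worse | 97–98% | 2.2–2.6% |
| Combination = LLLT, ultrasound 1.5 cm worse | 46% | 2.2% |
| Combination 1.5 cm worse than LLLT, 1.5 cm better than ultrasound | 91–93% | 0% |
| Combination 3 cm worse than both | 97–98% | 0% |
| Combination 3 cm better than both | 97–98% | 92–94% |
| Combination 2 cm better than both | 73% | 55–56% |
| Combination 3 cm better than one, 1.5 cm better than the other | 92% | 43–46% |
| Combination 1.5 cm better than both | 47% | 29% |

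At 3 cm the omnibus test rejects equally often when the combination is best, worst, or no better than LLLT.

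**4. Within-arm tests.** With a true mean change of 3 cm in an arm of 40, the Wilcoxon test is significant in over 99% of runs; with 1.5 cm, in 74%. Both hold whatever the other arms do. With no treatment effect and entry at VAS ≥4, regression to the mean alone gives a significant test in roughly 10 to 37% of arms, under an assumed pain mean of 5 to 6, SD 2 and correlation 0.5 to 0.7. This is illustrative only. Those inputs imply an SD of change of 2 × √(2 × (1 − r)), which is 2.0 at r = 0.5 and 1.5 at r = 0.7, not 3.49. The calculation also applies the cut to the analysed baseline score, whereas section 2.1 refers to pain in the previous 3 months.

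**The case against.** The strongest reply is that this is a condensed article. The between-group sentence could be meant as pairwise, follow-up tests after Kruskal–Wallis are often left to a full protocol or SAP, and one P column in an empty table does not rule them out. That stands so far: the article does not exclude pairwise testing. It does not remove the point, because the article positively names an omnibus test and a table layout that matches it, and both fall short of the stated aim. If pairwise testing is intended, the text does not say which comparisons are primary.

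A reader might infer that the plan intends to read a significant Kruskal–Wallis or within-arm result as proof of synergy. The article states no such rule and no success criterion at all, and it rests no efficacy claim on the within-arm tests. Table 2 would also show each arm's result, so a worse combined arm would be visible. The fault is that no stated test answers the question, not that a false reading is prescribed.

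A reader might also infer that beating both single modalities would show synergy. It would show added benefit. A more-than-additive effect needs a sham or untreated arm, and there is none.

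Finally, requiring both contrasts is one acceptable strategy among several (an adjusted post hoc procedure is another), and its cost in power can be large. That stands and is counted in the fix.

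**Conclusion.** The concern holds in this form: the tests named in section 2.7 and the single P value in Table 2 do not isolate either comparison that a claim for the combination needs. The figures of about 97% and 46% rest on 40 per arm, SD 3.49 and normal changes. The conclusion does not, because an omnibus rejection never identifies which arm differs. For scale, at 15 per arm the test still rejects in 62% of trials when the combination equals LLLT and ultrasound is 3 cm worse.

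The documents do not support saying that the sponsor will equate significance with synergy, or that pairwise tests are excluded. The regression-to-the-mean range is not an estimate for this trial, and the conclusion does not depend on it.

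**What to change.** In section 2.7, name two primary contrasts: combination minus LLLT, and combination minus ultrasound. Report each with an estimate and 95% CI (with rank tests, a Hodges–Lehmann shift would serve). Claim benefit only if both favour the combination at two-sided 0.05; no alpha split is needed because both must succeed. Keep Kruskal–Wallis as supportive. Make the within-arm Wilcoxon tests descriptive and say that no efficacy claim rests on them. Add two contrast columns to Table 2. Word the claim as added benefit over each single modality, not synergy.

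The text changes are small, but the power cost is not always small, because it depends on the smaller of the two contrasts. Against the omnibus test, the loss is about 4 to 5 percentage points if the combination is 3 cm better than both arms, about 17 points at 2 cm (73% − 56%), and 46 to 49 points if it is 3 cm better than one arm and 1.5 cm better than the other (92% − 46% and 92% − 43%). The sponsor should check that 120 patients suffice for the smaller difference it wants to detect.

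### The planned between-arm result for VAS is a single Kruskal–Wallis P value, with no estimate or interval for combined therapy against either single modality, so the size of any added benefit is left unquantified

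*Protocol article*

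**What the plan says.** All references are to the protocol article.

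- **Between-arm test (section 2.7).** "The difference between each treatment group is performed by the Kruskal–Wallis test". The article names no other between-arm analysis of VAS or WOMAC. The Wilcoxon signed ranks test in the same section compares baseline with post-treatment inside each group.
- **Criterion (section 2.7).** "The level of statistical significance is set as" P < .05.
- **Results table (section 2.6, Table 2, headed "Postoperative outcomes").** The shell has one column for each of the three arms and one P value column. It has no column for a difference or an interval.
- **Clinical benchmark (section 2.7).** "a clinically significant difference reduction in the VAS was defined as 3 cm". It is combined with "a standard deviation of 3.49" and "probability of a Type I error of 0.05 and power of 0.8" to give a sample size of 15, after which 120 patients are to be recruited. The article does not mention 3 cm again.
- **Hypothesis (Introduction).** "It is assumed that there will be a remarkable difference in postoperative outcomes between the intervention and control groups".

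**The concern.** The trial asks whether adding one modality to the other gives more pain relief than either alone. That question has two parts: combined against LLLT, and combined against ultrasound. A three-group Kruskal–Wallis test answers neither part directly. It tests whether the three arms differ somewhere, so it can be significant because the two single-modality arms differ from each other. It also gives no difference in centimetres.

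Two things are at stake. A significant P value could be reported as support for the hypothesised difference when the observed effect is well short of 3 cm, with no interval to show how large or small the true effect might be. A non-significant P value could be reported only as no difference found, although the data might be precise enough to rule out a 3 cm advantage. In both cases the trial would hold the information and the stated output would not report it.

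**Working it through.** **Inputs from section 2.7:** VAS difference 3 cm, SD 3.49, alpha 0.05, power 0.80, total 120. **Assumptions:** three equal arms, so 120/3 = 40 per arm (the ratio is not stated); no dropout; two-sided test (sidedness is not stated); 3.49 is the SD of VAS change (the article does not say); approximately normal change scores.

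**The article's own figure.** A two-sided two-sample comparison with these inputs needs 22 per arm, or 66 in all, not 15. A two-sided paired t calculation gives 12.68, rounded up to 13. Dividing 12.68 by 0.864, the minimum efficiency of the Wilcoxon test, gives 14.7, rounded up to 15. So 15 is matched exactly only as a within-group calculation. This bears on what the 3 cm means. No variant tried leads from 15 to 120 (15 × 3 = 45).

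**Pairwise cut-off.** SE = 3.49 × √(2/40) = 0.780. With t(0.975; 78) = 1.99, the smallest significant difference, which is also the 95% CI half-width, is 0.780 × 1.99 = 1.55 cm. 1.55/3 = 52%.

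**Three-group cut-off (ANOVA analogue).** d = √[F(0.95; 2, 117) × 2 × 3.49² / (40 × S)], where S is the sum of squared deviations of the arm means for d = 1.
- Two single-modality arms equal: S = 2/3, d = 1.68 cm (56% of 3 cm).
- One arm midway between the others: S = 1/2, d = 1.93 cm (64% of 3 cm).

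**Comparison with an ordinary design.** In a trial with 80% power, the cut-off is about 1.96/(1.96 + 0.84) = 70% of the target difference. It is lower here because 40 per arm exceeds the 22 needed; power for 3 cm is 97%.

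**What a negative result would show.** A pairwise interval lies below 3 cm when the observed difference is under 3 − 1.55 = 1.45 cm. With no true difference this happens in about 97% of trials. The table below comes from 4,000 simulated trials per row, with 40 per arm and one arm shifted. The interval compares the shifted arm with one other arm.

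| True difference (cm) | Kruskal–Wallis P < .05 | Among non-significant trials, upper 95% limit below 3 cm |
|---|---|---|
| 0 | 4.9% | 98% |
| 1.0 | 22% | 85% |
| 1.5 | 46% | 74% |
| 2.0 | 73% | 61% |
| 3.0 | 97% | 34% (of only 113 trials) |

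**Sensitivity.** With 32 per arm (20% loss, assumed) the half-width is 1.74 cm, or 58% of 3 cm, and 3 cm is excluded when the observed difference is below 1.26 cm. With SD 2.5 (assumed) and 40 per arm, the pairwise cut-off is 2.5 × √(2/40) × 1.99 = 0.559 × 1.99 = 1.11 cm. With Bonferroni adjustment over three pairs at SD 3.49, the half-width is 1.91 cm.

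**The case against.** - **An article may leave estimates and intervals to the full protocol or analysis plan.** This stands to a degree: a missing interval alone would be a weak point. But the article does fix the test, the criterion and the layout of the results table, and what it fixes is an omnibus P value that does not address the two contrasts of interest.
- **Arm-level values will be printed.** This stands. A reader might infer that the arms are never judged by size. The documents do not support that: setting alpha does not forbid describing the effect, and Table 2 has a column for each arm, from which a crude difference can be read. What is missing is a named contrast and its uncertainty.
- **A cut-off below the target difference is normal.** This stands. About 70% is usual, and the fall to 52% to 64% comes from recruiting more patients than the calculation requires. It is not an error in the test. The 1.55 cm figure also belongs to a pairwise comparison that section 2.7 does not plan; 1.68 to 1.93 cm applies to the planned one.
- **The 3 cm may not be a between-arm value.** This stands. Section 2.7 calls it a reduction, and the figure of 15 fits a within-group calculation. If it is a within-patient benchmark, the percentages of 3 cm lose their clinical meaning, and using it as a margin could wrongly dismiss a useful difference between two active treatments.

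**Conclusion.** The point holds as a gap between the trial's question and its stated output. The only between-arm result for VAS is one three-group P value, with no estimate or interval for combined therapy against LLLT or ultrasound. At 40 per arm and SD 3.49, significance is reached at 1.55 cm pairwise, or 1.68 to 1.93 cm on the three-group test. These are 52% to 64% of 3 cm.

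A reader might also infer that a negative result could not exclude 3 cm. The figures show otherwise. The half-width of about 1.55 cm that makes modest differences significant also lets most negative results exclude 3 cm: 98% of them at a true difference of 0, and still 61% at 2 cm. The limitation is in what is reported, not in the precision of the trial.

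The absence of an estimate or interval from the stated output does not depend on any assumption. The centimetre figures rest on equal allocation, no dropout and 3.49 being the SD of change. Reading them as fractions of a clinically important effect also requires 3 cm to be a between-arm value, which the article does not say. Severity is minor to moderate: the randomised comparison remains valid, and the remedy is cheap.

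**What to change.** 1. In section 2.7, name two contrasts in VAS change, combined minus LLLT and combined minus ultrasound, each reported with a 95% CI. If the rank analysis is kept, use the Hodges–Lehmann shift. Tie the contrasts to a stated time point, because the primary outcome in section 2.5 is weekly.
2. Add the two contrasts as columns in Table 2.
3. State that the size of effect will be described from these intervals, and that P < .05 remains the test that a difference exists.
4. State whether the 3 cm is a within-patient or a between-arm value. Discuss the intervals against it only if it is a between-arm value. If it is within-patient, do not use it as a margin between arms.

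The cost is a few sentences and two table columns. No new data are needed, and neither the sample size nor alpha changes. The downside is that some significant results will have to be described as small.
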